#### 2. Treatment

Two groups of 10 schistosomiasis patients each will be identified. Group (1) will be treated with Somatostatin (3.5 μg/kg/hour; single bolus and i.v. infusion for 24 hours) + Praziquantel (40 mg/kg). For somatostatin treatment the i.v. infusion will be started first; 3 mg somatostatin will be dissolved in the 1 ml of saline provided. This solution will be added to the saline transfusion unit and administered to the patient for the next 12 hours. Once finished the second packet of 3 mg somatostatin will be used similarly for a second saline transfusion unit for the remaining 12 hours. The bolus dose of 250 μg will be dissolved in the 1 ml of saline provided and administered over 90 seconds soon after the start of the i.v. infusion.

Group (2) will be treated with Propanolol + Praziquantel.

#### 3. Data analysis

Survival graphs will be set up to correlate somatostatin administration with survival time.

The primary efficacy variable is the number of patients meeting the failure of therapy definition during the infusion period. Failure criteria are defined as death during infusion, persistence of active bleeding (The haemodynamic instability criteria points to the inability to achieve and maintain a systolic blood pressure of 80 mm Hg OR presence of a 20 mmHg drop in systolic blood pressure from the highest post resuscitation value AND achieving a heart rate of 120 bpm OR a 20 bpm increase from highest post resuscitation value OR Inability to achieve and maintain a Hct of – 27% of Hb of – 9 g/dl despite blood transfusion of 2 units or more.

The clinical criteria of active bleeding include hematemesis (fresh or semi fresh blood), hematochezia, melena.

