Conduct of trial – Active bleeding episode (haematemesis, haematochezia, melena) from a potential variceal source should be confimed by a medical team (the ER physician, the ICU physician, the investigator). Patients may be outpatients or already hospitalised patients. Patients will be randomised to either arm in a sequential manner. Randomisation, and the start of study drug infusion if in adjunctive therapy arm, should be accomplished as soon as possible following identification of a patient qualifying for the study and following the conduct of pre-randomisation study procedures.

Sample Size Criteria – Assuming a 80% chance of finding a significant difference <0.05 between the two study cohorts, the following statistics were established:

(A) If 99% of the untreated subjects and –

10% of somatostatin treated subjects bled -5 volunteers per group were sufficient;

20% treated subjects bled – 7 volunteers per group were required;

30% treated subjects bled-9 volunteers per group were needed.

(B) If 90% of untreated subjects bled, and –

10% of somatostatin treated group bled – 7 volunteers in each cohort were sufficient;

20% of somatostatin treated group bled – 9 volunteers in each group were required;

30% of somatostatin treated group bled – 10 volunteers in each group were needed.

(C) If 70% of untreated subjects bled, and:

10% of somatostatin treated group bled – 12 volunteers per group were sufficient;

20% of somatostatin treated group bled – 18 volunteers per group were required;

30% of somatostatin treated group bled – 28 volunteers per group were needed.

In cirrhotic patients with bleeding oesophageal varices somatostatin administration controls bleeding in more than 80% of the treated patients. Based on this report, we propose to start this pilot study with 10 subjects/group.

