#### 4. Control points

A two part questionnaire will be set up to control treatment outcomes. The pre-treatment part of the clinical questionnaire will identify inclusion criteria questions:

(1) When was the last haematemesis incidence?

(2) When did the present incident start?

The post-treatment part of the questionnaire will identify treatment outcomes. The following questions will be answered:

(1) What was the reaction to somatostatin infusion?

(2) When did bleeding stop after somatostatin infusion?

(3) GI disturbances: Is there abdominal pain, nausea, diarrhea, after somatostatin infusion?

(4) Control of early rebleeding: Is there early rebleeding in the 8 days following somatostatin administration?

(5) Control of late rebleeding: When is the next rebleeding incident? Subjects will be followed up on a monthly basis, by home visits.

(6) Control of mortality: Is there any difference in mortality time between the two groups.

(7) Control of fibrosis: Does ultrasonography detect anti-fibrotic effect of somatostatin after treatment?

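### The primary endpoint is counted over the infusion period, but only the somatostatin arm is described as having an infusion, so the control arm has no stated window

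*Protocol article*

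**What the plan says.** The primary variable is set in the protocol article, section 3 (Data analysis): "The primary efficacy variable is the number of patients meeting the failure of therapy definition during the infusion period". The definition of failure that follows uses the same clock for death: "Failure criteria are defined as death during infusion, persistence of active bleeding".

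Section 2 (Treatment) describes the two arms. Group 1 receives "Somatostatin (3.5 μg/kg/hour; single bolus and i.v. infusion for 24 hours) + Praziquantel (40 mg/kg"), and the text explains how the 24 hours are delivered as two consecutive 12-hour units. Group 2 has one sentence: "Group (2) will be treated with Propanolol + Praziquantel". It gives no infusion, placebo infusion, route, start time or duration.

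Section 1 (Selection of patients, under the conduct of the trial) confirms that the infusion depends on the arm. It asks that randomisation, and "the start of study drug infusion if in adjunctive therapy arm", be done as soon as possible once a qualifying patient has been identified and the pre-randomisation procedures are complete.

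**The concern.** A two-arm comparison of failure counts needs both arms observed over the same stretch of time, from a start that treatment does not influence. Here the stretch is defined by an event that belongs to one arm. The article does not leave the window open for a later document. It states a window, and that window does not fit the control arm described one section earlier.

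Two consequences follow. First, the control count depends on a start and a length that nobody has fixed. If they are chosen once results are visible, the choice can favour either arm. Second, randomisation and infusion start are separate steps, so a Group 1 patient who dies between them has not died during infusion and is not a failure under the rule. Such a patient has been randomised and belongs in the comparison.

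**Working it through.** The point is one of definition, so the check sets the relevant statements side by side.

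**Step 1. Does any section give the control arm a window?**

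| Place in the protocol article | Group 1 (somatostatin) | Group 2 (propranolol) |
|---|---|---|
| 1. Selection of patients, conduct of trial | infusion starts as soon as possible | infusion wording is conditional on arm |
| 2. Treatment | bolus plus 24-hour infusion | drug names only |
| 3. Data analysis, primary variable | infusion period | no equivalent |
| 3. Data analysis, death criterion | during infusion | no equivalent |
| 4. Control points, early rebleeding | timed from somatostatin | no equivalent |

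The last row refers to the questionnaire item "Is there early rebleeding in the 8 days following somatostatin administration". It is not the primary variable. It is listed because it is another place where a control-arm clock might have been found, and it supplies none.

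**Step 2. Do the sample-size figures imply a window?** Section 1 sets 80% power and a 0.05 level ("Assuming a 80% chance of finding a significant difference <0.05 between the two study cohorts"), without naming a test or its sidedness. The check took the smallest n per group for which the summed binomial probability of all tables with more bleeding in the control group and two-sided Fisher p < 0.05 reaches 0.80.

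| Control v somatostatin bleeding | Stated n per group | Recomputed n per group |
|---|---|---|
| 99% v 10 / 20 / 30% | 5 / 7 / 9 | 5 / 7 / 9 |
| 90% v 10 / 20 / 30% | 7 / 9 / 10 | 7 / 9 / 12 |
| 70% v 10 / 20 / 30% | 12 / 18 / 28 | 12 / 18 / 29 |

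All nine agree within 2 patients. None of the rates carries a time horizon, so this section cannot supply the missing window.

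**Step 3. What would an analyst have to decide?** The text is compatible with at least three starts for Group 2: randomisation, the first propranolol dose, or a time matched to infusion starts in Group 1. It fixes no length for Group 2 either.

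**Step 4. Do the choices treat like patients alike?** Take a patient who dies after randomisation and before any study drug.

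- In Group 1, under the stated rule, the death is not counted.
- In Group 2, with a window from randomisation, the death is counted. The arms are then treated differently, and the difference favours somatostatin.
- In Group 2, with a window from the first propranolol dose, the death is not counted. The arms then agree, but each has lost a randomised patient's outcome.

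With 10 patients per group, each patient so affected is 1/10 = 10 percentage points of that arm's failure proportion. The documents do not say how many patients might be affected or how long the gap before infusion would be, so the calculation stops here.

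**The case against.** The strongest reply is that the intent is plain. The trial compares two groups, the infusion has one fixed length, and a sensible reader would apply the same 24 hours to controls. The document also never says outright that propranolol is not infused. Part of this stands: 24 hours is the natural length. But no section says that it applies to Group 2, and the start would still be open. If propranolol were infused, its duration would still be unstated.

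It can also be said that counting patients as randomised is an analysis-set rule usually left to the analysis plan. That is fair, and its absence is not criticised here. It appears in the fix because a window starting at randomisation works only if such patients stay in the count.

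A reader might infer more than the text supports:

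- **That no control patient could ever fail (0 of 10).** This literal reading conflicts with the evident two-group intent and with control bleeding rates of 70% to 99% in the sample-size scenarios.
- **That the survival curves share the fault.** The sentence "Survival graphs will be set up to correlate somatostatin administration with survival time" names the exposure of interest, not time zero, and the Control points section asks about mortality time between the two groups.
- **That events after an infusion stopped early are lost.** The documents do not mention early stopping.
- **That bleeding before the infusion is lost.** Active bleeding is a condition of entry. If it continues into the infusion it is still counted. What the rule loses is chiefly a death in that gap.
- **That one patient moved across the boundary measures the bias.** Two-sided Fisher p is 0.023 for 2/10 v 8/10 and 0.070 for 2/10 v 7/10, but this shows only that small tables are fragile near 0.05. The plan's own 20% v 90% case, 2/10 v 9/10, gives p = 0.0055. A one-patient shift leaves it significant (2 v 8, p = 0.023; 3 v 9, p = 0.020). The article names no Fisher test in any case.

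**Conclusion.** The point holds in a limited form. The primary variable and its death criterion are timed by an infusion that only Group 1 is described as receiving, so the window does not apply to Group 2 as written. A Group 1 death between randomisation and infusion start would also go uncounted.

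This rests on one inference: that Group 2 receives no study infusion. The silence of the Treatment section and the arm-conditional wording in section 1 both support it.

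The size and direction of any bias cannot be derived from the documents. The gap before infusion is meant to be short, and nothing shows how many outcomes a different window would move. It would therefore go too far to call the comparison biased. What can be said is that the primary comparison is not fully defined, and that the missing part could be filled in after outcomes are seen.

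**What to change.** Before the first patient is randomised, make three wording changes in section 3 (Data analysis):

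1. Define the primary efficacy variable as failure of therapy within a single window that starts at randomisation and has the same length in both arms. Twenty-four hours would match the stated infusion; the sponsor should confirm the length.
2. State that every patient is counted in the arm to which he or she was randomised, including a patient who dies before study drug is started.
3. Replace the criterion of death during infusion with death within that common window.

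The case report form should record the time of randomisation and the time of each failure event in both arms.

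The cost is wording in the protocol and the case report form. The number of patients, the treatments and the schedule of care are unchanged.

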### Study design

#### 1. Selection of patients

Age and Morbidity criteria – Adolescent subjects, age range varying from 12–17 years will be selected. The inclusion criterion will be schistosomiasis patients with bleeding from oesophageal varices in the last 24 hours. A random selection will be made to form two groups, a study group and a control group. Control of active infection will be done by means of CAA-strips on urine or blood. Subjects will be asked to fill in an informed consent form and the pre-treatment part of a questionnaire.

The inclusion criteria will be established fibrosis due to schistosomiasis of clinical history, physical examination and laboratory findings (and an examination compatible with the presence of portal hypertension due to fibrosis). Clinically active upper gastrointestinal bleeding (haematemesis of fresh or semi fresh blood and/or melena and/or haematochezia) with or without haemodynamic instability (systolic blood pressure < 80 mm Hg and heart rate > 120 bpm) will be selected. Subjects must be male or non-pregnant, non-lactating female subjects. Females of childbearing potential will have to utilize contraception for the duration of the study. Written or verbal documented informed consent will be needed from all subjects.

Exclusion criteria will include participation by subjects in another investigational study within the last 14 days. Subjects may not undergo treatment with endotherapy, i.e. band ligation, sclerotherapy or other (balloon tamponade). Treatment with somatostatin, vasopressin or their analogues will also be a exclusion criteria. Subjects with end stage liver disease with hepatorenal syndrome, diffuse hepatocellular carcinoma, patent porto-systemic shunts, known diagnosis of non-fibrotic portal hypertension, severe cardiovascular diseases, i.e. acute myocardial infarction and heart failure will be excluded. Concurrent use of metoclopramide is also not advised.

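### The primary failure rule reuses the entry bleeding signs without saying when they become persistence, whether they suffice alone, or what window applies in the propanolol arm

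*Protocol article*

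**What the plan says.** **Entry.** Section 1 (Selection of patients) asks for "schistosomiasis patients with bleeding from oesophageal varices in the last 24 hours" and then for "Clinically active upper gastrointestinal bleeding (haematemesis of fresh or semi fresh blood and/or melena and/or haematochezia", with or without haemodynamic instability. Its paragraph on the conduct of the trial adds: "Active bleeding episode (haematemesis, haematochezia, melena) from a potential variceal source should be confimed by a medical team". Randomisation, and the start of the infusion where it applies, "should be accomplished as soon as possible following identification of a patient qualifying for the study".

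**Primary endpoint.** Section 3 (Data analysis) states: "The primary efficacy variable is the number of patients meeting the failure of therapy definition during the infusion period". It continues: "Failure criteria are defined as death during infusion, persistence of active bleeding". A parenthesis opens at that point and is never closed. It holds the blood pressure, heart rate and haematocrit/haemoglobin criteria. A separate paragraph follows: "The clinical criteria of active bleeding include hematemesis (fresh or semi fresh blood), hematochezia, melena".

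**Window.** Section 2 (Treatment) gives the somatostatin arm a 24-hour infusion. For the control arm it names propanolol and praziquantel and describes no infusion.

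**The concern.** The signs that bring a patient into the trial are the signs listed for failure. Patients are to be randomised quickly after identification, so the presenting bleed may still show itself when the endpoint window opens. Melena or semi-fresh haematemesis in the first hours can be blood lost before any treatment. The definition has nothing that separates this from bleeding that treatment did not stop: no hour, no requirement for a new episode, and no statement that a sign must be joined by another criterion.

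Two things are at stake. If carried-over signs count, failures are added in both arms. Most are added in the arm with more controlled patients, so the difference shrinks. If they are left to judgement, similar cases can be scored differently, and the article gives no rule to keep scoring alike in the two arms. With 10 patients per arm, a few reclassified patients change the result.

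**Working it through.** **1. Entry and endpoint side by side**

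| Item | Entry (section 1) | Failure (section 3) |
|---|---|---|
| Signs | haematemesis (fresh or semi-fresh), melena, haematochezia | the same three |
| Timing | active and confirmed, also within the last 24 hours | during the infusion period, no start time for signs |
| Haemodynamic instability | may be present or absent | a listed criterion |
| Link between signs and other criteria | not needed | not stated |

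Only the signs duplicate the entry condition. The haemodynamic and Hct/Hb criteria do not.

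**2. The plan's own figure.** Section 1 gives 9 per group for 90% v 20% (80% power, 0.05) and chooses 10 per group. The pooled normal formula, two-sided, gives 7 per group without continuity correction and 10 with it. Exact two-sided Fisher power is 83% at 9 per group and 84% at 10. The chosen size therefore fits these rates, and the sample-size table is not the problem here.

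**3. Inputs for the sensitivity check**
- Control failure 90%: one of the article's scenarios, given there for untreated subjects who bled.
- Somatostatin failure 20%: the same scenario, in line with the article's statement that more than 80% of treated cirrhotic patients are controlled.
- 10 per arm, from sections 1 and 2.
- Two-sided Fisher test at 0.05: assumed, as sidedness and test are not stated.
- q, the share of patients with controlled bleeding who are scored as failures on residual signs alone: assumed, equal in both arms, shown as a range.

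**4. Formula.** Observed failure p' = p + (1 − p)q. For q = 0.2:
- control: 0.90 + 0.10 × 0.2 = 0.92
- somatostatin: 0.20 + 0.80 × 0.2 = 0.36
- difference: 0.56, against 0.70 at q = 0; in general it is 0.70 × (1 − q)

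Power is the sum of binomial probabilities over all pairs of counts with Fisher p < 0.05.

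| q | Control | Somatostatin | Difference | Power |
|---|---|---|---|---|
| 0 | 90% | 20% | 70 points | 84% |
| 0.1 | 91% | 28% | 63 | 73% |
| 0.2 | 92% | 36% | 56 | 61% |
| 0.3 | 93% | 44% | 49 | 49% |
| 0.5 | 95% | 60% | 35 | 24% |
| 1 | 100% | 100% | 0 | 0% |

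**5. Other base rates in the article.** At q = 0.5, power is 35% for 99% v 20% (98% at q = 0) and 10% for 70% v 20% (43% at q = 0). The direction is the same, and the size depends on the base rates.

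**The case against.** The strongest reply is that the rule speaks of persistence, not presence. A sign that is there when the clock starts has not yet persisted. The criteria in the parenthesis all need elapsed time: pressure achieved and maintained, change from a post-resuscitation value, Hct/Hb not held despite transfusion. One can read the signs as establishing active bleeding and the parenthesis as establishing its persistence. On that reading, carried-over melena alone is not failure.

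This stands against the stronger inference that a reader might draw, that every patient is a failure at time zero and both arms must reach 100%. The text does not say that. It is the extreme of one possible reading. What remains is that the article does not choose between the readings, and that persistence is given no duration on either.

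A reader might also infer that an open-label team will decide each case. The article states neither the blinding status nor who scores failure. The medical team that it names confirms bleeding at entry. An infusion described in one arm only makes knowledge of the arm plausible, no more.

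The article condenses a fuller protocol, which could carry operational detail. But it prints this definition with numeric limbs and a window, so the objection is to what is printed.

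Section 4 (Control points) asks when the present incident began and when bleeding stopped after somatostatin infusion. That helps in part, but the second question names somatostatin only, and neither is tied to the failure rule.

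Finally, q has no source in the article, and the 90% refers to untreated subjects while the controls receive propanolol. The table shows sensitivity, not an expected loss.

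**Conclusion.** The point holds as a badly fixed definition of the primary endpoint. The failure rule repeats the entry signs, sets no time at which a continuing sign becomes persistence, leaves open whether signs alone suffice, and uses a window that the control arm does not have.

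If signs alone suffice, misclassifying even 10% of controlled patients takes power from 84% to 73%, below the article's 80% target. At 50% it is 24%. Power reaches zero only if every controlled patient is so scored. These figures rest on 90% v 20%, 10 per arm, a two-sided Fisher test and an assumed share equal in both arms. At 99% v 20% the design withstands more: power is still 80% at q = 0.25. If the signs must be joined by a haemodynamic or Hct/Hb criterion, this loss does not follow from signs alone, but the wording and the window still need to be settled.

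**What to change.** Rewrite the failure definition in section 3 (Data analysis) so that it:

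1. sets the assessment window from randomisation, with the same length in both arms, in place of the infusion period;
2. states the time after randomisation, chosen by the sponsor's clinicians and common to both arms, from which bleeding signs count towards failure, with earlier signs counting only if a haemodynamic or Hct/Hb limb is also met;
3. closes the parenthesis and states the AND/OR structure that joins death, signs, haemodynamic limb and Hct/Hb limb;
4. requires the death, sign-based, haemodynamic and Hct/Hb components to be reported separately by arm, so that a result driven by residual signs can be seen.

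The cost is endpoint wording and a recorded time for each bleeding sign in both arms. The question in section 4 on when bleeding stopped can serve if it is asked in both arms and linked to the rule. There are two downsides. An early bleed that stops before the chosen time is no longer a failure on signs alone. Old blood passed after that time may still be misclassified.

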#### 4. Control points

A two part questionnaire will be set up to control treatment outcomes. The pre-treatment part of the clinical questionnaire will identify inclusion criteria questions:

(1) When was the last haematemesis incidence?

(2) When did the present incident start?

The post-treatment part of the questionnaire will identify treatment outcomes. The following questions will be answered:

(1) What was the reaction to somatostatin infusion?

(2) When did bleeding stop after somatostatin infusion?

(3) GI disturbances: Is there abdominal pain, nausea, diarrhea, after somatostatin infusion?

(4) Control of early rebleeding: Is there early rebleeding in the 8 days following somatostatin administration?

(5) Control of late rebleeding: When is the next rebleeding incident? Subjects will be followed up on a monthly basis, by home visits.

(6) Control of mortality: Is there any difference in mortality time between the two groups.

(7) Control of fibrosis: Does ultrasonography detect anti-fibrotic effect of somatostatin after treatment?

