Complications linked to hepato-intestinal schistosomiasis are increasing in the area of Richard-Toll, Northern Senegal. These cases are being identified at the local health centre. However, considering the high prevalence of schistosomiasis in this region, it is likely that the number of severe cases is much higher. Clear guidelines for the management of such severe complications and criteria for referral and surgery are required in this region. The establishment of an algorithm on how to treat these patients and create the appropriate infrastructure is urgently needed. The priority is how to take care of these patients and more so what is the best way of doing this under local conditions. One of the first steps is to critically evaluate the Niamey-Belo-Horizonte ultrasound methodology in patients with severe periportal fibrosis. Efficient management of bleeding varices in the afflicted patients is imperative.

Given the background that somatostatin is an ideal vasoactive drug in the field of liver pathology, it is our opinion that somatostatin will be more efficacious and safe as compared to currently used beta blocker drugs like propanolol, in the control of acute oesophageal variceal bleeding due to *Schistosoma mansoni *infection. Moreover using this neuropeptide may increase time to failure of drug treatment, decrease incidences of early re-bleeding (day 4, 8) and incidences of death during the follow up period. Decreased frequencies of late rebleeding (days 30, 60, 90) may occur, all indicating the safety of using somatostatin. Praziquantel cover would be given to all study patients.

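### Both tolerability questions, and two bleeding questions, are worded for somatostatin only, so read literally the control arm gives no reaction or gut-symptom data

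*Protocol article*

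**What the plan says.** Section 4 (Control points) of the protocol article lists seven post-treatment questions and says they will be answered. Two concern tolerability:

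- Item 1: "What was the reaction to somatostatin infusion"
- Item 3: "GI disturbances: Is there abdominal pain, nausea, diarrhea, after somatostatin infusion"

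Two bleeding items are tied to the same drug. Item 2 asks when bleeding stopped after the infusion, and item 4 asks "Is there early rebleeding in the 8 days following somatostatin administration". Item 7 asks whether ultrasound shows an anti-fibrotic effect of somatostatin. Only item 5 (next rebleeding) and item 6 (mortality time in the two groups) fit both arms as worded.

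Section 2 (Treatment) describes the control arm in one line: "Group (2) will be treated with Propanolol + Praziquantel". No infusion is described for that arm.

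The Background gives the opinion that "somatostatin will be more efficacious and safe as compared to currently used beta blocker drugs like propanolol" in acute variceal bleeding from this infection. It then lists longer time to failure, fewer early rebleeds, fewer deaths and fewer late rebleeds, and closes with "all indicating the safety of using somatostatin". It also says "Praziquantel cover would be given to all study patients".

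**The concern.** A statement that one treatment is safe compared with another needs the same symptoms recorded in the same way in both arms. As worded, the reaction and gut-symptom items can be completed only for patients who had the somatostatin infusion.

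Two things would be lost. First, any symptoms on propranolol would go unrecorded by these items. Second, all patients take praziquantel and all enter with upper gastrointestinal bleeding. Abdominal pain, nausea or diarrhoea after the infusion could come from either of these, and only the control arm's answers could show how much does.

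The Background does not fill the gap. Death is a fair safety outcome. Rebleeding and time to failure measure whether the treatment works, so fewer rebleeds say nothing about whether it is tolerated.

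**Working it through.** The plan gives no figure on this point. The check is a comparison of texts, followed by simple arithmetic on what could be learned with and without control-arm answers.

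**Step 1. Which items can be answered for group 2 as worded?**

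| Item | Subject | Names somatostatin | Fits group 2 as worded |
|---|---|---|---|
| 1 | Reaction | Yes | No |
| 2 | Time bleeding stopped | Yes | No |
| 3 | Gut symptoms | Yes | No |
| 4 | Early rebleeding | Yes | No |
| 5 | Next rebleeding | No | Yes |
| 6 | Mortality time | No | Yes |
| 7 | Ultrasound, fibrosis | Yes | No |

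Five of seven items name somatostatin, including both tolerability items. The only safety outcome left with data from both arms is mortality (item 6).

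**Step 2. What is known about the arm difference without control answers?**

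Input: 10 patients per group (sections 1 and 2). Let x somatostatin patients report gut symptoms. The unseen control proportion can be anything from 0 to 1, so the difference (somatostatin minus control) lies between x/10 - 1 and x/10.

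- x = 0: -100 to 0 percentage points
- x = 3 (an illustration, not a figure from the plan): -70 to +30 percentage points

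The span is always 100 points. This holds for any unobserved proportion; it simply says that the data carry no comparison.

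**Step 3. What is known if both arms are asked?**

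Wilson 95% limits for x of n, with p = x/n and z = 1.96:

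(p + z²/2n ± z·√(p(1-p)/n + z²/4n²)) / (1 + z²/n)

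- 3 of 10: (0.3 + 0.192 ± 1.96·√(0.0210 + 0.0096)) / 1.384 gives 10.8% to 60.3%.
- 0 of 10: the lower limit is 0 and the upper limit is 0.384/1.384 = 27.8%.

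The Newcombe interval for a zero difference with equal arms is ±√((p - lower)² + (upper - p)²).

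- 3 of 10 in each arm: √(0.192² + 0.303²) = 0.359, so -35.9 to +35.9 points.
- 0 of 10 in each arm: √(0² + 0.278²) = 0.278, so -27.8 to +27.8 points.

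**Step 4. How often would a symptom be seen at all in 10 patients?**

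The chance of at least one event is 1 - (1 - p)^10. For assumed true rates of 5%, 10% and 20% it is 40%, 65% and 89%. Two-arm answers make a comparison possible, but at this size they can only describe.

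**The case against.** The strongest reply is that the list is shorthand and not a final form. Item 6 asks about a difference between groups and item 7 about an anti-fibrotic effect; no patient could answer either, so form items and study questions are mixed. The Abstract and the Discussion both expect rebleeding to be delayed relative to the control group, which would make no sense if early rebleeding went unrecorded there. Loose drafting explains items 1 and 3 equally well. The safety statement is an opinion in the Background, and section 3 (Data analysis) names an efficacy variable and survival graphs, with no comparative safety test.

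Much of this stands. It limits the point to what happens if the questions are used as printed. It does not remove it, because the article prints the questions and says they will be answered, and nothing stated corrects the one-arm wording.

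Four stronger readings are tempting and are not supported:

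- **That no comparative safety statement could be made.** Mortality is asked about in both groups and is a fair safety outcome. What would be lost is comparative tolerability.
- **That the trial collects no adverse events in controls.** General adverse-event collection may sit in the full protocol, which is not shown.
- **That the plan will attribute shared symptoms to somatostatin in an analysis.** No such analysis is described. The risk lies in how one-arm symptom data would be interpreted.
- **That heart rate in the failure definition extends the problem to the primary endpoint.** The definition includes "AND achieving a heart rate of 120 bpm OR a 20 bpm increase from highest post resuscitation value", and a beta blocker may lower heart rate. But the document does not give the size or direction of any effect. It also does not exclude beta-blocker use in group 1, so an effect confined to controls is not established. How the definition's conditions combine is a separate question and no part of this point.

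**Conclusion.** The point holds in a limited form. As printed, items 1 to 4 refer to a drug that group 2 does not receive. Followed literally, the control arm yields no reaction or gut-symptom data. Apart from mortality, the Background's opinion on safety against propranolol could not be examined, and symptoms from praziquantel or from the bleed could not be told apart from those of somatostatin.

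The size is a difference left open over 100 percentage points, against roughly ±28 to ±36 points in the two illustrations once both arms are asked. The conclusion assumes that the printed wording is what will be used and that no other form records these symptoms in controls; the document cannot settle either. The primary endpoint is not affected.

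The phrase about safety at the end of the Background passage may attach to late rebleeding alone or to the whole preceding list. On either reading it counts an efficacy outcome as evidence of safety.

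**What to change.** - Ask items 1 to 4 identically in both arms, worded as *after the start of study treatment*, and at the same times, for example 24 hours and day 8. Counting from the start of assigned treatment avoids relying on an infusion that is described for group 1 only.
- Assess item 7 (ultrasound) in both arms.
- Report tolerability and mortality by arm, descriptively and without a test.
- Treat rebleeding and time to failure as efficacy outcomes, and do not cite them as evidence of safety.

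The cost is the rewording of a few questions and slightly more data collection in 10 control patients. The change belongs before the first patient, because symptoms not asked about at the time cannot be reliably recovered later. The downside is that the comparison stays imprecise at 10 per arm, and the report should say so.
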